#### Data Collection, Monitoring and Follow-Up Details

All data collected are being recorded by good clinical practise trained nurse researchers on standardised data sheets as performed previously in our many RCTs (44–46). Most women and their infants are followed in their local community/region where the infants also receive their routine vaccinations following the national infant immunisation schedules for either Australia or Malaysia (Table 2). Immunisations are confirmed by checking the Australian Immunisation Register and the infants' individual paper-based health records in Malaysia.

**Table 2 T2:** Infant immunisation schedules for the Northern Territory and Queensland, Australia and Sabah, Malaysia.

**Age**	**First Nations infants, Australia**	**Other Australian infants^*^**	**Sabah, Malaysia**
Birth	HB	HB	HB
			BCG
2-months	DTaP-IP-HB-Hib	DTaP-IP-HB-Hib	DTaP-IP-HB-Hib
	PCV-13	PCV-13	PCV-13
	Meningococcal B	Rotavirus	
	Rotavirus		
3-months			DTaP-IP-HB-Hib
4-months	DTaP-IP-HB-Hib	DTaP-IP-HB-Hib	PCV-13
	PCV-13	PCV-13	
	Meningococcal B	Rotavirus	
	Rotavirus		
5-months			DTaP-IP-HB-Hib
6-months	DTaP-IP-HB-Hib	DTaP-IP-HB-Hib	Measles
	PCV-13		PCV-13
9-months			MMR
12-months	PCV-13	PCV-13	MMR
	Meningococcal B	Meningococci A,C,W,Y	
	Meningococci A,C,W,Y	MMR	
	MMR		

* *Maori and Pacific Island infants*.

*HB, hepatitis B; BCG, Bacille Calmette-Guerin; DTaP-IPV-HB-Hib, diphtheria-tetanus-acellular pertussis-inactivated poliomyelitis vaccine-hepatitis b-Haemophilus influenzae type b; PCV-13, 13 valent pneumococcal conjugate vaccine*.

At enrolment, maternal baseline specimens [blood, nasopharyngeal swabs (NPS)] and demographic/clinical data are being collected (e.g., age, gender, family and household size, tobacco smoking, family and immunisation history, medications, co-morbidity) from the woman and their medical notes. Participants are contacted at least monthly using a variety of communication tools [telephone, short messaging service (SMS) texting, emails and/or home visits].

Women are seen at delivery and specimens (blood, NPS) collected. Infants are followed for 12-months with specimens collected at birth (cord blood, NPS). The infants are also seen with additional specimens collected (when possible) at ages 6-months (clinical review, blood, NPS) and 12-months (clinical review, blood, NPS).

Infants' data are obtained from parents/carers and the medical notes at every visit (birth details, breast feeding, growth, respiratory symptoms/signs and ALRIs co-morbidities). We have established robust methods for capturing ALRI episodes from our previous RCTs (44, 45, 47). Hospital records will be reviewed for identifying hospitalisations. We are also contacting the infants' primary care physician for verification of ALRIs. Adverse events (see below) are recorded following the current guideline definitions (19).

*Exit criteria* are: consent withdrawn, infant born with congenital disorders affecting ALRI frequency (e.g., chromosomal abnormalities, genetic syndromes, primary immuno-deficiency, airway, cardiac or neuromuscular disorders), or death.

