Many pathogens cause ALRI in young children. Globally, *Streptococcus pneumoniae* (pneumococci) is reported to be the largest contributor to deaths annually from ALRIs in all age groups [55.4% or 1.52 million (95% UI 858,000–2.18 million)], including children <5-years of age [55.8% or 393,000 (95%UI 228,000–532,000)] (1). Also, pneumococci remain the most common cause of community-acquired pneumonia in adults (23). Unsurprisingly, pneumococcal infection was one of the most common ALRIs in high-income countries before pneumococcal conjugate vaccines (PCV) were introduced (24). As Australian First Nations children and adults have an increased risk of ALRI and pneumococcal infection, they have a different immunisation schedule to other Australians (20) and had PCVs several years earlier than other community groups (3, 25). Currently, Northern Territory First Nations children receive a 13-valent PCV (PCV-13 or Prevenar-13) at 2, 4 and 6-months of age as their primary course and a booster dose at age 12-months (3 + 1 schedule), while all adults aged ≥50-years receive PCV-13 followed by two doses of the 23-valent pneumococcal polysaccharide vaccine (PPV-23) 5-years apart (20). In contrast, the national immunisation program schedule for other Australians is two doses of PCV-13 at 2 and 4-months of age with a booster at 12-months (2 + 1 schedule) and a single dose of PCV-13 at age 70-years (20). Thus, the potential beneficial effects of protecting the infant against pneumococcal infections align with the data supporting a maternal immunisation strategy to reduce ALRIs, especially for First Nations infants.

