#### Secondary Lab Outcomes in a Subgroup of Infants (Estimated *n* = 70)

Vaccine-type pneumococcal IgGs [(maternal: baseline, birth); (infant: cord, 6-months and 12-months of age)];Cytokines from the infant's systemic immune responses *ex-vivo* (TNF-α, IFN-γ, IL-6, IL-13, IL-1β) from PBMCs stimulated with NTHi (51) and pneumococci (at least one each of vaccine and non-vaccine types); andNasopharyngeal carriage of NTHi and pneumococci [(maternal: baseline, birth); (infant: birth, 6-months and 12-months of age)].

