### For Secondary Aims

We will compare the inter-group proportion of children with any hospitalised ALRI, clinical pneumonia and radiographically-confirmed pneumonia using ORs with logistic regression (and 95%CIs). In addition, we will construct a Kaplan-Meier curve for each group for time-to-first ALRI episode and respiratory-related hospitalisation, perform a log-rank test and report a HR (using the Cox regression model).

For the secondary laboratory-based aims, we will compare between-group differences for: (i) IgG geometric means against PD (25) and serotype-specific pneumococci (31) using Student's T-test after logarithmic transforming the data (+/- maternal pre-vaccine levels adjustment); (ii) cytokine levels expressed by PBMCs after stimulation by live NTHi and pneumococci [Mann-Whitney (25, 51)]; and (iii) proportions of nasopharyngeal cultures positive for *H. influenzae* and pneumococci (vaccine and non-vaccine types) using Chi^2^ tests and reporting ORs (95%CIs) (44, 45).

The proportion of participants (pregnant participant and infants) with any adverse events will be compared between groups, using Chi^2^ tests and reporting ORs (95%CIs) (44, 45).

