Our RCT targeted First Nations peoples because of their known increased risk of ALRIs and their high prevalence of chronic lung disease in children (3, 7, 8). We also included Malaysian women for several reasons. Firstly, this will improve generalisability of our RCT by including a LMIC study centre. Secondly, at this site, there is relatively high mortality and morbidity from ALRIs, including pneumonia (65), and chronic suppurative lung disease is a recognised health problem (66). Finally, the senior researchers have established successful collaborations (47).

While First Nation children's immunisation coverage is generally high (>90%), it is often delayed (67). During this vulnerable period, robust immune responses are required to combat ALRIs. Vaccinating pregnant women provides infants with maternally-derived antibodies during the first 4-6 months of life (14, 16). This is a period of rapid lung growth where infectious insults may have long-term consequences by interrupting lung development and possibly also altering immune programming (68). Thus, host defences boosted by vaccine-induced maternal antibodies could protect the infant from early ALRIs and their late sequelae.

Preventing infant ALRI could also reduce subsequent hospitalisation. An Australian study found that ALRI in early infancy significantly increased the risk (HR = 3, 95%CI 2.6–3.4) for further respiratory hospitalisation after adjusting for risk factors (smoking, gestational age, season, delivery mode), with a dose-response effect (54).

There are eight published maternal immunisation studies using PPV-23 in the third trimester. None have shown any clinical benefit for respiratory infections (18, 31). The newer PCVs are more immunogenic and effective than the 3-decade old PPV-23 (14, 23). Our reasons for choosing PHiD-CV, instead of other types of PCVs, were provided in the Introduction. Furthermore, we are using a single PHiD-CV dose (rather than multiple doses) for our RCT as a single dose of PCV induces robust T-cell responses and B-cell memory in adults (23) and older children (27). Studies show that antibody responses against vaccine serotypes are above the WHO-defined immune correlate of protection level threshold of 0.35 ug/ml (27) and current guidelines recommend single PCV doses in adults (18, 20, 23). This is in contrast to the multiple doses required for priming infants (27) who have immature immunity.

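### The t-test for infant serotype-specific IgG at 6 and 12 months ignores three PCV-13 schedules that differ at those ages, which costs precision in about 70 infants

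*Protocol article*

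**What the plan says.** Under Data Collection, Monitoring and Follow-Up Details, infant sampling after birth is set by age: "The infants are also seen with additional specimens collected (when possible) at ages 6-months (clinical review, blood, NPS) and 12-months". The IgG outcome follows the same clock: "Vaccine-type pneumococcal IgGs [(maternal: baseline, birth); (infant: cord, 6-months and 12-months of age". The laboratory subgroup is estimated at 70 infants.

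The Introduction gives the two Australian PCV-13 schedules. Northern Territory First Nations infants receive it "at 2, 4 and 6-months of age as their primary course and a booster dose at age 12-months", and other Australian infants receive "two doses of PCV-13 at 2 and 4-months of age with a booster at 12-months (2 + 1 schedule". Table 2 applies the second schedule to Maori and Pacific Island infants and adds a third for Sabah, with doses at 2, 4 and 6 months and none at 12 months. On First Nations children's immunisation, the Discussion says that "it is often delayed (67".

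Under For Secondary Aims, IgG geometric means are compared between arms "using Student's T-test after logarithmic transforming the data", with optional adjustment for the mother's pre-vaccine level. No other term is named. Randomisation is stratified by site. Infant vaccinations are checked against the Australian Immunisation Register or, in Malaysia, paper health records.

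**The concern.** An infant PCV-13 dose is expected to move that infant's serotype-specific IgG, whatever the mother received. If samples labelled with one age come from infants with different dose histories, the spread of log IgG within each arm includes a component unrelated to allocation. A t-test leaves all of it in the error term.

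In about 70 infants that is worth avoiding. The article promises no power for the IgG comparisons, so no claim is broken. The cost is a wider confidence interval for the geometric mean ratio at 6 and 12 months than the same samples could give.

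**Working it through.** **Schedules against sampling ages (Table 2)**

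| Infant group | PCV-13 ages (months) | Doses by the 6-month blood, if on time | Doses by the 12-month blood, if on time |
|---|---|---|---|
| Australian First Nations | 2, 4, 6, 12 | 2 or 3 | 3 or 4 |
| Maori and Pacific Island | 2, 4, 12 | 2 | 2 or 3 |
| Sabah | 2, 4, 6 | 2 or 3 | 3 |

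Where two counts appear, they depend on whether the dose due at that age came before the blood. Late doses lower the counts and shift the time since the last dose. At 12 months the groups differ even if every infant is on time and bled before any dose due: two earlier doses for Maori and Pacific Island infants, three for the others. At 6 months, on-time infants bled before any dose due would all have had two, so differences there arise only from doses already given or from delay.

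**Which IgG results are affected.** Cord and maternal bloods precede any infant PCV-13 dose. The Introduction says PCV-13 is conjugated to CRM197, so it does not present protein D. Only infant serotype-specific IgG at 6 and 12 months remains.

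**Size.** The article gives no SD, effect size, post-dose share or power for IgG, so there is no figure of its own to reproduce; its 88% power concerns the ALRI rate. The following is an illustration on assumed inputs.

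Treat each sample as pre-dose or post-dose. Let s be the SD of log10 IgG among samples with the same dose status, q the post-dose share and F the fold rise after a dose.

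- Added variance = q(1 − q)(log10 F)²
- Standard error ratio = √[1 + q(1 − q)(log10 F)²/s²]
- Effective number of infants = 70 / ratio²

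Assumed ranges: s 0.4 to 0.5, q 0.3 to 0.5, F 2 to 6.

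| s | q | F | Added variance | SE ratio | Effective n |
|---|---|---|---|---|---|
| 0.5 | 0.3 | 2 | 0.21 × 0.0906 = 0.0190 | √(1 + 0.0190/0.25) = 1.04 | 65 |
| 0.5 | 0.3 | 4 | 0.21 × 0.3625 = 0.0761 | √(1 + 0.0761/0.25) = 1.14 | 54 |
| 0.4 | 0.5 | 4 | 0.25 × 0.3625 = 0.0906 | √(1 + 0.0906/0.16) = 1.25 | 45 |
| 0.4 | 0.5 | 6 | 0.25 × 0.6055 = 0.1514 | √(1 + 0.1514/0.16) = 1.40 | 36 |

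With a lower share, q = 0.1, and F = 4, added variance is 0.09 × 0.3625 = 0.0326. The ratio is then 1.06 for s = 0.5 and 1.10 for s = 0.4.

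**The third row as power.** Assume 35 infants per arm and two-sided 5% significance. With s = 0.4, the geometric mean ratio detectable at 80% power is 10^[(1.96 + 0.84) × 0.4 × √(2/35)] = 1.85. The mixed SD is √(0.16 + 0.0906) = 0.501, which raises it to 2.16. Power for the ratio of 1.85 falls to 61%.

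These figures are for all dose-status variation together. A schedule-group term recovers only the part lying between schedules; the rest needs dose count and timing.

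**The case against.** Much of the opposing case stands.

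- **Draw order.** Whether blood is taken before or after a dose at the same visit is detail that an article may leave to the full protocol (version 7, not shown). It also matters little. The Introduction puts a robust IgG response at about 4 weeks (said of pregnant women), so blood taken just after a dose is still effectively pre-dose. What matters is doses given earlier elsewhere, or late.
- **Assumed inputs.** The post-dose share, SD and fold rise are all assumed. Delay tends to push the dose due at 6 or 12 months past the blood, which lowers the post-dose share.
- **A legitimate estimand.** IgG at a fixed age under routine schedules is a reasonable pragmatic comparison, and the text already allows one covariate.
- **Left to the analysis plan.** A detailed analysis plan is promised, and covariates often belong there. But the article goes further than silence: it names the test and its only covariate, and the test fits the described sampling poorly.

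Two stronger readings are tempting. A reader might infer that the arm comparison is biased or confounded. The documents do not support that: allocation is randomised within site, which separates Sabah from Australia, and schedules and dose timing should balance between arms in expectation.

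A reader might also infer that the samples certainly mix pre-dose and post-dose bloods, and that this hides blunting of the infant's own vaccine response. Mixing is possible, not shown. The article gives no figures for a maternal effect before and after an infant dose. It answers the interference worry with a preliminary safety analysis at 6 months, and it states the antibody aim in the Discussion in terms of maternal and cord blood.

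**Conclusion.** The point holds as a matter of precision in a secondary laboratory outcome. Infant serotype-specific IgG at 6 and 12 months is sampled by age across three schedules that differ at those ages, and the stated test has no term for schedule or dose history.

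On the assumed ranges (s 0.4-0.5, 30-50% of samples post-dose, 2- to 6-fold rise), the standard error is about 4-40% larger than with uniform dose status. At a 4-fold rise it is 14-25% larger, which leaves the precision of about 45-54 infants out of 70. At a 10% post-dose share it is 6-10% larger. The direction is secure; the size is not, because no input comes from the documents. The primary outcome is untouched.

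**What to change.** Under For Secondary Aims, replace the t-test for 6- and 12-month infant serotype-specific IgG with a linear model on log IgG. It should contain treatment arm, infant schedule group (Australian First Nations, Maori and Pacific Island, Sabah) and maternal pre-vaccine level, and report the adjusted geometric mean ratio with its 95% CI. Schedule group follows from the infant's identity and site, and the randomisation strata capture it only in part: the inclusion criteria admit infants on both Australian schedules, so one Australian site may hold both.

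Add a supporting model with the number of PCV-13 doses received and days since the last dose, taken from the vaccination records already being verified. These variables arise after randomisation, so this model should stay secondary.

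The cost is small. With 70 infants, residual degrees of freedom fall from 70 − 2 = 68 to 70 − 5 = 65 in the main model. No new data are needed, and neither the vaccine schedules nor the visits change. Reordering blood and vaccine within a visit is not needed as the main remedy. Cord, maternal and protein D IgG need no change on this account.

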### Laboratory-Based Methods

#### NPS Bacteriology

NPS are stored and processed as described previously (38, 44, 48). Batches of swabs will be thawed and cultured on selective media. Growth of pneumococci and *H. influenzae*, including NTHi, will be confirmed by standard techniques (43, 44). *H. influenzae* will be differentiated from *H. haemolyticus* isolates by targeting the *siaT* gene using real-time polymerase chain reaction assays (49). Pneumococcal serotypes will be determined later by Quellung serotyping methods (50).

#### Peripheral Blood Mononuclear Cell (PBMC), NTHi and Pneumococcal Driven Systemic Immune Responses

In all, 2–3 mls of blood collected are processed and cryopreserved as described previously (25, 51) using standardised methods. We have established previously the preparation of the NTHi inoculum, cell culture and immunoassays (25, 51). Briefly, PBMC (1 × 10^6^ cells/ml) will be challenged with live NTHi or pneumococci (4 × 10^6^ colony forming units/ml), phyto-hemagglutinin (PHA; positive control) or medium alone (baseline control). Stored bronchoalveolar lavage (BAL) isolates (48) that are proven viable will be used. We will use two non-vaccine pneumococcal serotypes (15A, 15B) and two vaccine-type serotypes (19F, 23F), the commonest serotypes found in our BAL studies (48).

Cytokines, representative of the innate (TNF-α), Th1 (IFN-γ) and Th2 (IL-6, IL-13) immune responses and regulation of inflammation (IL-1β,) will be measured in culture supernatants at 24 or 72-h, as optimised previously, using a Dissociation-Enhanced Lanthanide Fluorescence Immunoassay (DELFIA™) (51, 52). Additional cytokines may be performed pending new data at the point when the specimens are analysed at the end of the study. DELFIA™ has a large dynamic range (~ 3–30,000 pg/ml) with low background interference. All samples for immunology-related work will be batch-tested to minimise inter-assay variation.

#### Serum IgG Measurements

Total serum IgG antibodies specific for PD and selected pneumococcal serotypes (both vaccine and non-vaccine types, yet to be determined) will be undertaken using methods described previously in our studies (25, 31).

### Outcomes

All clinic staff (other than the nurse administering the study vaccine) and persons collecting the outcome data are blinded to the mothers' allocation group. Our main outcomes are at 12-months as ALRIs early in life increase the risk for subsequent hospitalisations for ALRIs later in infancy (53–55) and it is a more robust outcome for comparative epidemiological studies.

Our case definition of ALRI is a medically-attended episode of illness defined as the presence of acute cough, dyspnoea, raised respiratory rate for age, new abnormal chest examination findings or abnormal radiographic findings for presumed respiratory illness (clinic visits for ALRIs within 2-weeks of each other will be counted as part of the same ALRI episode).

*The primary outcome* is the rate of medically-attended ALRIs at age 12-months of our endpoint case definition that fulfils any of the below, i.e., a composite single outcome:

Case definition confirmed via medical records;Case definition suspected via medical records (i.e., some information in the above is missing and the case definition above cannot be confirmed); orCase definition based upon parent reported ALRI: parent reports a medically-attended episode of a respiratory illness for which antibiotics were prescribed.

We also plan a sensitivity analyses based on episodes meeting the criteria of

(i–iii) with antibiotics prescribed.(i) and (ii) only.(i) only.

#### Secondary Clinical Outcomes

Pneumonia confirmed by chest radiograph with: (a) antibiotics given (b) no antibiotics given;Clinical pneumonia defined as cough or difficulty breathing for <14-days accompanied by: raised respiratory for age (>60 breaths per minute if aged 0 to <3-months, ≥50 breaths per minute for those aged 3 to 12-months), lower chest wall indrawing, nasal flaring, grunting, dull chest percussion note, coarse crackles, or bronchial breathing, peripheral oxygen saturation <92%, altered consciousness, inability to sit or feed, convulsions (56) with: (a) antibiotics given (b) no antibiotics given;Hospitalised ALRI episodes with: (a) antibiotics given (b) no antibiotics given;Time-to-first ALRI episode (defined as medically-attended ALRI with antibiotics prescribed) and respiratory-related hospitalisation;Proportion of children with any medically-attended ALRI;Adverse events related to vaccination, pregnancy and infants (as separate outcomes) using definitions outlined by the GAIA series of papers (19).

#### Secondary Lab Outcomes in a Subgroup of Infants (Estimated *n* = 70)

Vaccine-type pneumococcal IgGs [(maternal: baseline, birth); (infant: cord, 6-months and 12-months of age)];Cytokines from the infant's systemic immune responses *ex-vivo* (TNF-α, IFN-γ, IL-6, IL-13, IL-1β) from PBMCs stimulated with NTHi (51) and pneumococci (at least one each of vaccine and non-vaccine types); andNasopharyngeal carriage of NTHi and pneumococci [(maternal: baseline, birth); (infant: birth, 6-months and 12-months of age)].

#### Halting Rules

The study is being monitored by an external independent data safety and monitoring committee (iDMC) with predefined halting rules for harm. This includes increased adverse events in the mother, foetus or infants, or if the difference between groups at the interim analysis (when 50% of the sample size participants have each provided at least 6-months of data) reaches a *p* ≤ 0.01.

#### Data Monitoring, Management and Analyses

All adverse events, including serious adverse events, are monitored by an iDMC, which was established and met prior to commencing the study. A First Nations Reference Group based at the Menzies School of Health Research in Darwin oversees the cultural aspects of the study. Data coding and entry is coordinated in Brisbane and conducted in accordance with good clinical practise.

The analyses will be overseen by a biostatistician. Results will be reported and presented in accordance with CONSORT guidelines. We will use the “intention-to-treat” approach for the main analyses. We also plan a “per-protocol” analysis. A detailed statistical analysis plan will be developed prior to undertaking the final analysis. Any exploratory, *post-hoc* or unplanned analysis will be identified clearly.

